### Recruitment, Assignment, and Allocation

Women are recruited using on-site clinic, community-based, and Web-based strategies. At the clinic, nurses identify potential eligible women and refer them to a study staff member who is ready in the waiting room to speak with them about the study and, if interested, screen them for eligibility. Community-based recruitment includes hanging study flyers at local businesses, churches, campus, and community centers. Web-based recruitment occurs through the study website [33] and Facebook ads. Interested women call a toll-free number. A project staff member explains the study, obtains verbal assent to ask questions, and determines eligibility based on the inclusion criteria described above. Pregnant women with overweight and obesity are recruited between 8 and 12 weeks gestation and randomized to the intervention or control condition until about 36 weeks gestation. The study biostatisticians developed a randomization scheme using variable size, random permuted blocks to ensure the number of participants in each group is balanced after each set of *B* randomized participants, where *B* is the block size. Randomization to intervention (n=15) or control (n=15) groups uses 1:1 allocation; participants are entered consecutively. When a woman is eligible and informed consent is signed, a staff member requests randomization by a unique participant identification number.

### Conceptual Framework

We used principles from the Theory of Planned Behavior [34] and self-regulation [35] for the conceptual framework of the Healthy Mom Zone Intervention (Figure 2).

The Theory of Planned Behavior assumes a person is motivated for a behavior (eg, managing GWG) when she has a positive attitude, believes that significant others want her to do the behavior (subjective norm), and has the perceived ability to do the behavior (perceived behavioral control) [34]. Self-regulation assumes that behavior is goal-directed and regulated by feedback control processes [35]. The participant engages in activities in which she can succeed, and this confidence in performance success can influence her perceived behavioral control. Thus, self-monitoring is a core strategy of behavior modification and a key aspect of the dynamical systems model to manage GWG in this study. The overall simulation model for GWG is depicted in Figure 3 and includes the following: (1) a 2-compartment energy balance model predicting changes in body mass as a result of energy intake and physical activity, (2) 2 Theory of Planned Behavior models describing how energy intake and physical activity are affected by behavioral variables, (3) a program delivery module relating magnitude and duration of components to inflows of the Theory of Planned Behavior models, and (4) 2 self-regulation units modeling how success expectancies in the intervention influence one’s goal achievement motivation [36,37]. This model serves a vital role in evaluating the decision rules in the individually tailored intervention and in applying advanced strategies to produce decision frameworks for making program adaptations.

**Figure 2 figure2:**
[figure not shown]
Conceptual framework for Healthy Mom Zone Intervention. HE: healthy eating; PA: physical activity, GWG: gestational weight gain.

**Figure 3 figure3:**
[figure not shown]
Energy balance model underlying the Healthy Mom Zone Intervention. TPB: Theory of Planned Behavior; I_1_…I_n_: Intervention components; i: exogenous variables that serve as inputs for behavioral models; y_i_: system outputs; ξ_1_: Behavioral belief × evaluation of outcome; ξ_2_: Normative belief × motivation to comply; ξ_3_: Control belief × power of control belief; I_1_: Healthy Eating Education; I_2_: Healthy Eating Weekly Plan; I_3_: Healthy Eating Active Learning; I_4_: Goal Setting; I_5_: Physical Activity Education; I_6_: Physical Activity Weekly Plan; I_7_: Physical Activity Session; I_8_: Daily Weight Scale; I_9_: Dietary Record; I_10_: PA monitor output. Black solid line shows input/output signals between models; Black dashed line shows self-regulation feedback loop; Blue dashed line shows intervention dosages which indicate how and when the intervention is adapted; Green dashed line shows tailoring variables that inform whether the intervention is adapted; Circle dashed line shows regular measurement of important outcomes (self-regulation intervention).

### Healthy Mom Zone Intervention Components

The intervention components (see Figure 4) are informed by past research and our own pilot data [5-10,31,32,38,39]. Evidence from model lifestyle interventions [8-10,38], GWG interventions [5-7], and our research on promoting healthy behaviors [39-41] shows education, goal-setting and action planning, and self-monitoring can effectively manage weight. Our past studies have shown that when people are taught how to set appropriate plans and goals, self-monitor, and manage their time, they are more likely to achieve their goals and see positive behavioral outcomes (eg, engage in healthy eating and exercise to manage weight) [39,42-44]. Furthermore, convincing evidence from past research [39,44,45-49] shows that healthy eating and physical activity active learning (eg, active participation in strategies to reduce energy density such as food preparation and planning, portion size control, increasing intake of fruits and vegetables, meeting physical activity goals, and engaging in guided exercise sessions) are effective for lowering energy intake and managing body weight. We also learned from our pilot study [50] that women wanted to know more about how the target intervention behaviors (eg, weight, physical activity, dietary intake) were related to their baby’s growth, so we developed brief modules to inform women about the following: (1) current research studies (Featured Evidence and Baby’s Health) and (2) unique aspects of their baby’s growth (Baby Fun Facts); content is delivered weekly in this study via email.

### Standard of Care Control Condition

All women in the study receive standard prenatal care (eg, regular visits and prenatal counseling with health care provider; provider is not informed by the research team of randomization assignment). The women randomly assigned to the control condition also complete the same measurement protocol as the intervention participants, which includes daily, weekly, and monthly assessments (see Table 1).

### Healthy Mom Zone Intervention Description

Women randomized to the intervention group receive the baseline dosage, which includes for all women the intervention components (described above) of education, goal-setting and action plans, featured evidence on baby’s health, baby fun facts, and self-monitoring. Participants meet weekly with a study dietitian and are given customized calorie goals and a booklet developed for this study that contain customized healthy eating plans, recipes, and tailored meals to meet calorie goals. They are also given a physical activity booklet with customized and safe pregnancy-related exercises (see Multimedia Appendix 1). A study staff member reviews each woman’s weight, physical activity, and dietary intake via real-time data collection procedures and generates a report for the study dietitian to review with the participant at the next intervention session.

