### Study Setting and Procedures

All participants, regardless of intervention assignment, complete the same study measurement protocol. The study setting includes onsite visits at the Penn State Clinical Research Center (University Park campus) and at-home participation. Interested and eligible women complete a preintervention assessment at the Penn State Clinical Research Center after the study is described and written consent is obtained. A study clinician assesses height, weight, blood pressure, and conducts a physical exam to identify health symptoms that may preclude study participation [29]. Women complete self-reported measures of their healthy eating/physical activity behaviors, knowledge, planned and self-regulatory behaviors, motivational determinants, demographics, and dietary intake using onsite paper and pencil and Web-based data capture software (Research Electronic Data Capture) [51].

Women then complete an air displacement plethysmography body composition assessment following a standardized protocol that takes approximately 30 min. Participants complete these same measures again at the postassessment at approximately 36 weeks gestation. In addition, during the course of the study all women are given a Wi-Fi scale for wireless uploading of daily weight, food scale to monitor daily intake, and log to record food and beverages (and amounts) consumed, and 2 monitors (wrist-worn activity monitor worn daily; waist-worn accelerometer worn in 2-week cycles) to track physical activity. Participants are asked to use these mHealth devices continuously over the course of the entire study. Women track dietary intake on 2 weekdays and 1 weekend using a mobile phone app. Measures are obtained at baseline, during the intervention (daily, weekly, and monthly), and postintervention. All participants are compensated up to US $420 in check or gift card for the pre and post, weekly, and monthly assessments over the study period. In addition, the intervention participants get to keep their Wi-Fi weight and food scales at the end of the study (control participants return them), and they receive a US $20 check if they attend 90% (25/28) or more of the intervention sessions.

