### Data Analysis

To establish initial validation of the intervention, contrasts constructed from linear mixed-effects models [54] will be used to assess differences between the intervention and control groups with respect to changes in continuous outcomes over time (from pre- to postintervention): changes in primary (GWG, energy intake, physical activity, planned/self-regulatory behaviors) and secondary outcomes (serum blood biomarkers, adiposity, knowledge). Linear mixed-effects models are an extension of ordinary regression models that account for within-subject variability inherent in longitudinal studies. Generalized estimating equations [55] with a logit link will be used to assess differences between the intervention and control groups with respect to dichotomous outcomes over time. If deemed necessary, confounding variables (eg, prepregnancy weight, age, obstetric complications) will be included as covariates. With respect to the participants meeting individual GWG goals based on prepregnancy BMI status [1], we will look at each woman and determine whether she met her GWG goal. We will code participants as “0” for GWG within goal, +1 for GWG over goal, and −1 for GWG under goal. A chi-square test will be used to assess differences between the intervention and control groups on this 3-level ordinal variable (ie, −1,0,1) assessing individual GWG goals. All hypothesis tests will be 2-sided, and analyses will be performed using SAS software version 9.4 (SAS Institute Inc., Cary, NC) or R software (R Foundation for Statistical Computing, Vienna, Austria).

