Modeling development and simulation are done in Matlab with SIMULINK (The MathWorks, Inc., Natick, MA). Functional data analysis modeling for time-varying modeling will rely on SAS. Weight predictions based on a first-principles energy balance model can be performed using measurements of a participant’s energy expenditure (physical activity and resting metabolic rate) and energy intake. Alternatively, energy intake can be estimated from the energy balance model using the measured weight gain and physical activity, which can then be compared with self-reported data [56,57]; this information can be used by dieticians to provide informative health guidance. Intensive measurements of the Theory of Planned Behavior constructs are used to build participant-based dynamical models using semiphysical model identification techniques. The integration of these behavioral models with energy balance models can be used to evaluate and implement decision policies based on control systems engineering for an intensively adaptive intervention, specifically Hybrid Model Predictive Control [37,58].

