### Strengths and Limitations

There are several positive features of this study. This study has strong public health relevance and clinical significance for the future management of GWG. We have also incorporated several innovative aspects into the study, including the use of (1) novel decision rules to choose when and how to adapt the intervention, (2) mHealth tools for self-monitoring of behaviors and real-time data collection to provide feedback to the participants, and (3) a unique computerized applet to generate individualized weight gain trajectories for comparing actual weight to the Institute of Medicine guidelines. In addition, customized eating and physical activity plans developed for this study aid in reducing participant barriers to engaging in healthy behaviors during pregnancy. Moreover, the intensive longitudinal data collection protocol allows for a myriad of systems approaches in support of implementing and evaluating intensively adaptive interventions [25,56-58]. Intensive data collection enables the application of system identification and state estimation approaches from engineering that, in turn, build comprehensive dynamical models for GWG used in adaptive intervention optimization. These methods can be used to estimate and correct energy intake over time, despite some missing data.

There are also some limitations of this research. The small sample size, although adequate for examination of the primary outcome (GWG), precludes the ability to make assumptions at a population level. Moreover, the target population is a homogenous sample of women from largely rural and suburban areas in Central Pennsylvania, thus limiting the extension of the study findings to more culturally diverse and urban populations of pregnant women with overweight and obesity. We do plan to understand the application of Healthy Mom Zone to a more diverse sample of pregnant women in the future, including those who are normal weight, more culturally diverse, and reside in varied communities across the United States.

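### Energy intake is compared between arms on what appears to be self-report, under reporting conditions that differ by arm, and the model-based check the article describes is not tied to that comparison

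*Protocol article*

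**What the plan says.** **The outcome.** Data Analysis uses contrasts from linear mixed-effects models to compare the arms on pre- to postintervention change, listing "changes in primary (GWG, energy intake, physical activity, planned/self-regulatory behaviors" as primary. Participants and Sample Size and Outcome Measures name GWG alone as the primary outcome. The measure behind energy intake is not named.

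**The instruments.** Study Setting and Procedures states "Women track dietary intake on 2 weekdays and 1 weekend using a mobile phone app". At the preintervention visit, "Women complete self-reported measures of their healthy eating/physical activity behaviors, knowledge, planned and self-regulatory behaviors, motivational determinants, demographics, and dietary intake" are collected, and the same measures are repeated at about 36 weeks. Table 1 marks the phone app as weekly. It also lists remote food photography, at postintervention and postpartum only.

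**The arms.** Healthy Mom Zone Intervention Description, on the intervention arm: "Participants meet weekly with a study dietitian and are given customized calorie goals". Beyond weight and activity, what staff review there for each woman is her "dietary intake via real-time data collection procedures and generates a report for the study dietitian to review with the participant at the next intervention session". On controls, Standard of Care Control Condition says: "The women randomly assigned to the control condition also complete the same measurement protocol as the intervention participants". It describes no calorie goals and no dietitian sessions for them.

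**The model-based alternative.** Data Analysis later notes that "energy intake can be estimated from the energy balance model using the measured weight gain and physical activity", that this estimate can be compared with self-reported data, and that dietitians can use the information for guidance. Strengths and Limitations adds: "These methods can be used to estimate and correct energy intake over time, despite some missing data".

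**The concern.** Both arms use the same instruments but not under the same conditions. An intervention woman knows that her intake data will be discussed with a dietitian who has also given her a calorie goal. A control woman has neither. That can change what is written down as well as what is eaten. It may lead to omitted or understated entries, or coaching may make the records more complete, so the direction of the bias is not known.

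A difference in recorded intake would then mix eating with reporting. The trial could credit the program with lowering intake when only the reporting changed, or miss a real reduction. This matters beyond the present sample. The study is meant to inform a later efficacy trial, and energy intake is an input to its dynamical model of weight gain. A larger sample would not remove the bias.

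**Working it through.** **1. What the contrast estimates.** Let Δ be the true arm difference in intake change, and b_I and b_C the average reporting-error changes in the two arms. The expected difference in recorded change is Δ + (b_I − b_C). Identical instruments do not make b_I equal b_C when goals and review exist in one arm only.

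**2. Is the measure self-report?** Data Analysis does not say, so this is an inference. The intake sources are the app record and the self-reported measures at the two visits. The abstract also lists energy intake among the weekly measures, and the app is the weekly intake instrument in Table 1. Food photography has no preintervention time point, so it cannot supply a pre-to-post change.

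**3. The plan's own power figure, for context.** Inputs from Participants and Sample Size: n = 12 per group, standardized difference 1.2, two-sided 0.05, 80% power for GWG. Two-sample t-test, df = 2 × 12 − 2 = 22, noncentrality = 1.2 × √(12/2) = 2.94: power is 0.802. The stated 80% reproduces. No SD or power is given for energy intake.

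**4. Effect of a differential bias.** Same test, Δ = 0, noncentrality = b × √6, where b is the assumed differential misreporting in SD units:

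| Assumed b (SD) | Chance of a significant arm difference |
|---|---|
| 0 | 5.0% |
| 0.2 | 7.6% |
| 0.4 | 15.5% |
| 0.5 | 21.6% |
| 0.8 | 46.6% |

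In kcal, an assumed differential of 200 kcal/day with an assumed SD of 600 to 300 kcal/day is 0.33 to 0.67 SD, giving about 12% to 35%.

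**5. A benchmark for a meaningful intake difference.** The Introduction cites an earlier lifestyle trial with gains of 23 and 30 pounds, a difference of 7 lb. Assuming 3,500 kcal/lb and 28 weeks (8 to 36 weeks' gestation, this trial's length): 7 × 3,500 = 24,500 kcal; 24,500 / (28 × 7 = 196 days) = 125 kcal/day. Against an assumed 2,000 to 2,500 kcal/day, this is 125/2,000 = 6.3% to 125/2,500 = 5%. So a differential misreporting of 5% to 6% would be as large as that benchmark. At an assumed SD of 600 to 300 kcal/day, 125 kcal/day is 0.21 to 0.42 SD, and the false-positive chance is about 8% to 16%.

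**6. Can the check be run in both arms?** Table 1 schedules daily home weight, a daily wrist activity monitor and a weekly metabolism device, and its caption applies the schedule to all participants. The back-calculation sentence needs weight gain and physical activity, so the inputs are collected in both arms.

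**The case against.** **The authors already anticipate misreporting.** This stands in part. The article says modelled intake can be compared with self-report and can correct intake over time. A reader might infer that a planned back-calculated measure is being left unused. The documents do not support that: it is offered as a possibility, with the comparison to self-report included. What is missing is narrower, namely any link to the between-arm contrast.

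**The intake measure is an operational detail for a fuller document.** Fair as far as naming goes; silence alone would be no finding. But this article lists the outcome as primary, describes reporting conditions that differ by arm, and describes a check. Those stated elements are not connected.

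**The reviewed data may not be the outcome.** A reader might infer that the dietitian-reviewed app record is the endpoint and that it is checked against the calorie goal. Neither is stated. The app has no pre or post mark in Table 1, a separate self-report exists at the visits, and goals and review are mentioned without being linked. The narrower point survives: the visit measure is also self-report, given by women who do or do not have goals and a dietitian. The staff feedback in the study overview is not limited to one arm, but it concerns device use and compliance.

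**Food photography could serve.** A post-only comparison of randomized arms needs no baseline, so this is possible, but the plan assigns it no such role.

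**Replacing recorded intake would be circular.** This stands. If weight gain differs at similar activity, modelled intake differs by construction. Making it the main comparison would largely restate the GWG result, so it belongs in a sensitivity analysis.

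**Conclusion.** The concern holds in limited form. Arm-dependent misreporting of energy intake is a credible bias, of uncertain direction, and the between-arm analysis as described has no safeguard against it. It rests on one strong inference, that the energy-intake outcome is self-reported.

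The size cannot be derived from the documents. The 8% to 22% range in false-positive chance assumes a bias of 0.2 to 0.5 SD. The 125 kcal/day figure rests on assumed conversion, duration and intake values and is a benchmark, not an estimate of the bias. A reader might infer that the trial's main result is at risk; it is not, because GWG is measured by scale. What is at stake is the claim about mechanism and what it carries into the later trial. This is a worthwhile, inexpensive improvement rather than a fault that threatens the study.

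**What to change.** In Data Analysis:

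1. State which energy-intake measure enters the mixed model.
2. Add the between-arm comparison of intake back-calculated from the energy balance model, with the same model in both arms, as a pre-specified sensitivity analysis.
3. Report the recorded-minus-back-calculated gap by arm, with a confidence interval for the arm difference.
4. Describe any difference in self-reported intake as an effect on reported intake, unless the gap is similar across arms and the back-calculated comparison agrees in direction.

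The cost is analysis wording and a model run per woman, with no new data. There are two limits. Back-calculated intake depends on measured weight, so it is not independent of GWG, and it carries the energy model's error. The gap comparison will also be imprecise: with 12 per arm the 95% half-width is 2.07 × √(2/12) = 0.85 of the gap's SD. The gap can therefore inform the wording of claims but cannot show that reporting was equal.

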**Figure 4 figure4:**
[figure not shown]
Healthy Mom Zone Intervention components. Components in light blue are in baseline intervention and delivered throughout the duration of the intervention. Active Learning component is adapted depending on decision rules and gestational weight gain (GWG) evaluations. BMI: body mass index.

The dietitian plots weekly GWG using individualized charts that illustrate GWG within the context of the Institute of Medicine guidelines and discusses strategies to overcome barriers to managing weight and engaging in healthy eating and physical activity behaviors. Women in the intervention also complete a 15-min postintervention exit interview at their post assessment to provide their feedback and perspective on multiple aspects of their intervention experience (eg, likes and dislikes about using the mHealth tools, adaptive dosages, active learning activities, completing study measures). Intervention sessions are randomly audio-recorded and coded for fidelity.

